#### Supportive control group

Supportive control groups are often used in PTSD treatment studies because they offer both a treatment (in contrast to a waiting list control group) and at the same time are less effective than state-of-the-art treatments (between d = 0.8; 26). We implement a control group with social support in a group format that has a long tradition in all Amcha centres. As described above, it is called “social club” and has the goal of exploring and strengthening the participants’ individual and social resources when talking about current interpersonal problems, personal decisions and plans and hopes for the future. It is a meeting place which answers the need to meet other people and take part in social interaction. It provides activities like films, lectures, courses in art, music, memory improvement, gymnastics, languages (English, Yiddish), visits to interesting places, birthday celebrations, discussions of relevant issues, etc. Importantly, there are no trauma-focused interventions in the supportive group. This is a fundamental difference to the treatment group. Taken together, participants in the control group receive supportive attention, which is ethically acceptable since the participant’s need to talk and relate is met. At the same time, using this control group is methodologically appropriate because the likelihood of a treatment effect is expected to be smaller than that in the LRT group. Moreover, recruitment of study subjects will not be compromised when using this control group. Members of the staff of Amcha, who are independent of the LRT interventionists, will provide the control intervention. Control group members may receive LRT or other psychotherapy after the follow-up assessment.

Records are kept in regard to which social club meetings each participant (treatment and control group) has attended in order to be able to monitor the type and frequency of social club meetings.

### Assessment

#### Eligibility screening

Before inclusion into the study, diagnostic interviews are conducted by student research assistants with experience and training in the assessment of PTSD, depression, anxiety disorder, prolonged grief disorder and related disorders, and in the administration of structured interviews. The following self-report measures are used in the context of a clinical interview:
PTSD: The PTSD Checklist for the “Diagnostic and Statistical Manual of Mental Disorders 5” (DSM-5) (PCL-5) is used [29]. It is a 20-item self-report measure that assesses the 20 DSM-5 symptoms of PTSD. It also makes it possible to come to a probable PTSD diagnosis according to DSM-5 criteria [30]. The questionnaire has been found reliable and valid in an Israeli sample [31].Depressive disorder: The Patient Health Questionnaire (PHQ-9) is a widely used 10-item self-report measure of depressive symptoms with well-established psychometric properties [32]. It makes it possible to diagnose a probable major and minor depressive disorder [33] and is sensitive to change [34]. The Hebrew version has also been found to be reliable and valid [35].Prolonged grief disorder is diagnosed according to the criteria proposed for the “International Classification of Diseases 11” (ICD-11) [36]. The validated Hebrew version is used [37].

To screen for potential cognitive impairment, the MMSE [38] in its Hebrew version [39] is used. The clinical work prior to registration will include anamnesis, family history, psychiatric, neurological, internal status and neuropsychological testing (MMSE).

#### Study outcome measures (primary and secondary endpoints)

All scales are applied in Hebrew language and have been tested for validity and reliability in this language. Primary endpoints are PTSD and depressive symptoms:
PTSD symptoms: The PTSD Checklist for DSM-5 (PCL-5) is used [29] in its Hebrew version [31], a 20-item self-report measure that assesses the 20 DSM-5 symptoms of PTSD.Depressive symptoms: The Patient Health Questionnaire (PHQ-9) and the Geriatric Depression Scale (GDS) are used. The PHQ-9 is a widely used 10-item self-report measure of depressive symptoms with well-established psychometric properties [32] in its Hebrew version [35]. The GDS is a 15-item self-report measure developed for use with older people [40]. It has been found reliable and valid in an Israeli sample [41].

Secondary endpoints are:
Grief symptoms: The ICD-11 Symptom-Diagnostic Test for Prolonged Grief Disorder (PG-ICD-11) questionnaire is a self-report measure of grief symptoms based on the proposal for the diagnostic assessment of PGD for ICD-11 [42]. It includes two core symptoms (yearning, preoccupation) and five additional symptoms (e.g. anger, survivor’s guilt). There has been research on the optimum symptom threshold [43]. The Hebrew version is used [37].Complex PTSD symptoms: The complex PTSD part of the ICD-11 Trauma Questionnaire [44] is used to measure complex PTSD symptoms. This 16-item measure captures four symptom clusters with two relating to affect regulation characterised by hyper-activation or deactivation, negative self-concept and disturbed relationships. The validated Hebrew version is used [37].Anxiety symptoms: The Depression Anxiety Stress Scale-21 (DASS-21) is a 21-item self-report questionnaire evaluating current anxiety, stress and depression levels [45] in its Hebrew version. The questionnaire has also been used in older people [46].Dysfunctional thoughts: The Posttraumatic Cognitions Inventory (PTCI) [47] assesses typical dysfunctional trauma-related thoughts and beliefs in the domains of negative cognitions about the self (21 items, e.g. “My life has been destroyed by the trauma”), negative cognitions about the world (7 items, e.g. “The world is a dangerous place”) and self-blame (5 items, e.g. “Someone else would not have gotten into this situation”). The questionnaire has been found reliable and valid in an Israeli sample [48].Reminiscence style: The Reminiscence Functions Scale (RFS) [49] is used to assess seven different reminiscence styles (boredom reduction, death preparation, identity/problem-solving, conversation, intimacy maintenance, bitterness revival, and teach/inform). A 28-item version has been shown to have the same factor structure [50]. We apply a Hebrew translation of the 28-item version [51].Positive well-being: The Life Satisfaction Index (LSI) [52] is used to measure positive aspects of well–being among older people. The LSI was intended to measure five components that had been identified in a review of previous measurement instruments. These include zest for life (as opposed to apathy), resolution and fortitude, congruence between desired and achieved goals, positive self-concept and mood tone. Positive well-being is indicated by the individual taking pleasure in his/her daily activities, finding life meaningful, reporting a feeling of success in achieving major goals, a positive self-image and optimism. The validated Hebrew version is used [53].Posttraumatic growth: The Posttraumatic Growth Inventory (PTGI) [54] measures positive change after traumatic experience on the following subscales (21 items): New possibilities, relating to others, personal strength, appreciation of life and spiritual change. The questionnaire is reliable and valid in an Israeli sample [55].

Outcome variables were assessed using these self-report instruments at three points in time (pretest, posttest, follow-up).

#### Predictors

Factors that might influence the endpoints will also be assessed:
Age at time of trauma (young age is associated with more symptoms)Gender (female gender is associated with more symptoms)Educational level, i.e. years of school educationCognitive status (assuming low status is associated with more symptoms)Trauma severity, i.e. number of traumatic events, months/years experiencing the Holocaust, incl. Critical life events in the previous 5 years.

In addition, several sociodemographic variables will also be included in the assessment, such as age, sex, family status, education and occupation.

#### Assessment of safety

Participants will be regularly screened for suicidality. In case of increased suicidality - although not expected - participants will be taken out of the study by the research team. For safety and for keeping an overview over the study, a case report form (CRF) will be completed after each information, assessment or therapy session. The CRF contains checklists, test results, information about the participant (other therapies, medications, problems etc.), adverse events, date of the assessments and name of the investigators.

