### Study objectives

To our knowledge, there is no controlled study evaluating the efficacy of psychotherapy in Holocaust survivors. Therefore, the general goal of this study is to evaluate the efficacy of an integrative, age-specific treatment of PTSD and related mental health problems (depression, anxiety, prolonged grief) in Holocaust survivors.

From the previous research outlined above follows that LRT, which not only meets the natural needs of older people to review their lives, but is also effective in the treatment of depression (as shown by several RCTs) and PTSD (as shown by case studies and preliminary results from one RCT), seems to be most promising for the treatment of Holocaust survivors.

Part of the basic support structure of Holocaust survivors in Israel are social support services, which are also provided by all Amcha centres throughout the country (called “social club”). The social clubs are meant to let survivors come together in an environment where they meet people with whom they share common experiences now and then. The clubs provide activities like films, lectures, courses in art, music, memory improvement, gymnastics, languages (English, Yiddish), visits to interesting places, birthday celebrations, discussions of relevant issues, etc. They are not intended for psychodynamic or trauma-focused psychotherapy.

Thus, in this study, participants receiving the treatment (LRT) are explicitly allowed to continue visiting the social club. The control group consists of social club member who receive no psychotherapeutic treatment (LRT or other). Control group participants might receive LRT after the follow-up assessment.

The goals of this study are:
to evaluate the effect of LRT for Holocaust survivors (LRT-HS), in addition to attending the “social club”, on symptoms of PTSD and related mental health problems (depression, anxiety, prolonged grief), compared to a supportive control group (“social club”);to identify groups of participants that seem to especially benefit from the treatment.

Two research questions will be investigated:
Does the LRT-HS as short-term treatment for Holocaust survivors, in addition to attending the “social club”, reduce the symptoms of PTSD and related mental health problems (depression, anxiety, prolonged grief) more than a supportive control group (only attending the “social club”)?

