## Methods/design

### Design

The proposed study is a randomised, controlled follow-up trial including Holocaust survivors with one or more stress-response disorders (i.e. PTSD, depression, anxiety and/or prolonged grief).

Participants will be randomly assigned (see Fig. 1) to either the LRT (in addition to the social club) or a supportive control group (social club only). The treatment includes 20–25 sessions. The participant timeline is presented as SPIRIT schedule in Fig. 1.

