**Fig. 1 Fig1:**
[figure not shown]
SPIRIT schedule of enrolment, treatment, and assessments. Abbreviations: DASS-21: Depression Anxiety Stress Scale-21; GDS: Geriatric Depression Scale; LSI: Life Satisfaction Index; MMSE: Mini Mental Status Examination; PCL-5: PTSD Checklist for DSM-5; PHQ-9: Patient Health Questionnaire 9; PTGI: Posttraumatic Growth Inventory; PTCI: Posttraumatic Cognitions Inventory; PTSD: Posttraumatic stress disorder; RFS: Reminiscence Functions Scale

Enrolment into one of the two groups will be done consecutively during the recruitment phase. The treatment phase takes approx. Nine months. Before and after the treatment phase, participants in both groups will be assessed. Follow-up will take place at 6 month post-treatment. All assessments will be conducted by blind assessors.

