#### Adverse events

Adverse events (AEs) are any negative medical or psychological occurrence in the study subject, e.g. worsening of symptoms. Serious adverse events (SAEs) are any negative and unexpected medical or psychological occurrence or effect that: results in death; is life-threatening (refers to an event in which the subject was at risk of death at the time of the event; it does not refer to an event which hypothetically might have caused death if it were more severe); necessitates hospitalisation, or prolongation of existing inpatients’ hospitalisation; results in persistent or significant disability or incapacity; is a congenital anomaly or birth defect.

Medical or psychological judgement will be exercised in deciding whether an AE is serious in other situations. Important AEs that are not immediately life-threatening or do not result in death or hospitalisation, but may jeopardise the subject or may require intervention to prevent one of the other outcomes listed in the definition above, will also be considered serious.

Reporting procedures: All adverse events will be reported. Depending on the nature of the event, the reporting procedures below will be followed. Any questions concerning adverse event reporting must be directed to the principal investigator in the first instance.
Non serious AEs: All such events, whether expected or not, will be recorded.Serious AEs: An SAE form will be completed and faxed to the principal investigator within 24 h. However, hospitalisations for elective treatment of a pre-existing condition do not need reporting as SAEs.

The principal investigator will assess whether the event is:
‘Related’, i.e. resulted from the administration of any of the research procedures; and‘Unexpected’, i.e. an event that is not listed in the protocol as an expected occurrence.

Reports of suspected related and unexpected SAEs (SUSARs) will be submitted within 15 days or within 7 days for fatal or life-threatening SUSARs, respectively, of the investigator becoming aware of the event to the Ethics Committee.

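### The form that records adverse events is triggered by therapy sessions that only the LRT arm has, so adverse event counts by arm would be open to ascertainment bias

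*Protocol article*

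**What the plan says.** The protocol article's Assessment of safety section names the safety record and its triggers: "a case report form (CRF) will be completed after each information, assessment or therapy session". Among the form's contents it lists "information about the participant (other therapies, medications, problems etc.), adverse events, date of the assessments and name of the investigators". A separate sentence in that section says "Participants will be regularly screened for suicidality", with no interval, assessor or arm.

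The arms differ in which of these contacts they have. Under Design, "The treatment includes 20–25 sessions"; the text with Fig. 1 adds that "The treatment phase takes approx. Nine months". Under Study objectives, control participants are social club members who receive no psychotherapy of any kind. Both arms have the same three assessments: pretest, posttest and a follow-up six months after treatment.

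For the social club, the Supportive control group section says "Records are kept in regard to which social club meetings each participant (treatment and control group) has attended", for the purpose of monitoring the type and frequency of meetings. It mentions no safety form there.

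The Adverse events section gives symptom deterioration as its example of an adverse event. It says of non-serious events that "All such events, whether expected or not, will be recorded", and it requires a serious event form within 24 hours. Neither rule is limited to an arm or a session.

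**The concern.** When adverse events are written down at contacts, the arm with more contacts records more of them, even if the true rates are equal. Here the extra contacts are the experimental treatment itself. A brief worsening in an LRT participant is likely to come up at the next session. The same episode in a control participant has no scheduled form until posttest, by which time it may have resolved and been forgotten.

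This matters because one LRT module is a narrative confrontation with the traumatic experience, so worsening during therapy is the natural safety question for this trial. If the session forms feed a count by arm, a real excess under LRT cannot be told apart from more frequent recording. The article's Detection bias paragraph does not help: it deals with outcome data at posttest and follow-up, not with adverse events noted after therapy sessions.

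**Working it through.** The article gives no figure for harms, so there is none to reproduce. The check has two parts.

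**1. Count the form-triggering contacts per arm.**

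Inputs: 20–25 therapy sessions in LRT (Design) and 0 in control (Study objectives); two assessments after baseline in each arm; a treatment phase of about 9 months; social club meetings not on the trigger list. Assumption: information sessions come before baseline and are equal in number in the two arms, so they drop out.

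| Period | LRT | Control |
|---|---|---|
| Between pretest and posttest | 20–25 | 0 |
| Posttest and follow-up | 2 | 2 |
| Total after baseline | 20 + 2 = 22 to 25 + 2 = 27 | 2 |

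Spread evenly over nine months, the LRT forms fall every 9/26 = 0.35 to 9/21 = 0.43 months. From posttest to follow-up the two schedules are the same, so the asymmetry is confined to the treatment phase.

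**2. Illustrate what unequal detection does to counts.**

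Formula: observed risk = true risk × detection probability. With equal true risk in both arms, the apparent risk ratio is the LRT detection probability divided by the control detection probability, whatever the true risk.

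Assumptions, none of them in the article: true risk of 20% or 40% in both arms; detection of 0.9 in LRT and 0.7, 0.5 or 0.3 in control. The planned 40 per arm at enrolment are used, without drop-out.

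| Control detection | Apparent risk ratio | Expected participants with an event, true risk 20% | Chance of a false LRT excess, true risk 20% | Expected participants with an event, true risk 40% | Chance of a false LRT excess, true risk 40% |
|---|---|---|---|---|---|
| 0.7 | 0.9/0.7 = 1.29 | 7.2 vs 5.6 | 7.0% | 14.4 vs 11.2 | 11.6% |
| 0.5 | 0.9/0.5 = 1.80 | 7.2 vs 4.0 | 17.5% | 14.4 vs 8.0 | 35.5% |
| 0.3 | 0.9/0.3 = 3.00 | 7.2 vs 2.4 | 37.7% | 14.4 vs 4.8 | 71.8% |

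The counts are 40 × true risk × detection; for example, 40 × 0.20 × 0.9 = 7.2. The chance column is a normal approximation for two proportions, tested at two-sided 5%, and counts significance in the direction of more harm under LRT. Without bias that chance would be about 2.5%. With equal detection (0.9 in both arms) the ratio is 1.00.

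**The case against.** Four points can fairly be made on the other side.

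**Control participants are not shown to be unmonitored.** A reader might infer from the trigger list that nobody looks at control participants for about nine months, or that suicidality is recorded only where the form is. The article does not support either reading. The screening sentence stands apart from the form and covers participants in general, and the rules on recording events and on 24-hour serious event reports apply to both arms. Nor is the form said to be the only route for an event to become known. This objection stands. What remains is that the article states a scheduled form for one arm during treatment and none for the other.

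**No harm comparison is planned in the article.** Its statistical section covers efficacy endpoints, and tabulation of harms is commonly left to an analysis plan. So it cannot be said that a planned comparison is biased, only that any count by arm built on these forms would be open to bias. The trigger list itself is stated, however, and it is asymmetric as stated; this is more than missing detail.

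**Much larger ratios are tempting but rest on extreme assumptions.** Suppose capture in LRT during therapy is complete, every event is transient, and an event is recalled only for w months before an assessment. Over nine months the apparent excess is then 9/w: 9-fold for w = 1 and 3-fold for w = 3. Over 15 months it is (9 + w)/(2w): 5-fold and 2-fold. Deaths and hospitalisations do not fade in this way, and persistent worsening is picked up equally in both arms by the symptom scales at posttest and follow-up. These ratios are limiting cases, not estimates.

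**Fig. 1 and the full protocol are not shown** and may give a schedule for both arms. If so, the trigger list still needs to agree with it.

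**Conclusion.** The concern holds in a limited form. Followed as written, the article's rule produces 20–25 adverse event forms in LRT and none in control between pretest and posttest, and 22–27 against 2 after baseline. These counts follow directly from the text, given only that information sessions are equal between arms.

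The consequence is conditional. If adverse event counts are compared by arm, they are open to ascertainment bias, probably in the direction of apparent harm under LRT and mainly for transient non-serious events. An apparent risk ratio of about 1.3 to 3 with no true difference follows from the detection values assumed above; the article gives no basis for choosing among them. Serious events and persistent worsening should be much less affected.

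This deserves a change because the cure is cheap. It does not bear on the efficacy endpoints and is not evidence that participants in either arm are neglected.

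**What to change.** 1. At the existing posttest and follow-up assessments, elicit adverse events in both arms with the same structured questions and the same fixed recall window.
2. Base any between-arm comparison on these answers, plus deaths and hospitalisations over the whole interval.
3. List events known only from therapy-session forms separately, and do not compare them between arms.
4. Reconcile the trigger list under Assessment of safety with the screening sentence in the same section and with the reporting rules under Adverse events, so that the text says how both promises are carried out in the control arm.

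Attaching the form to social club meetings would not solve the problem: both arms may attend the club, and LRT would keep its session forms on top.

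The cost is protocol wording and a short question set at two visits. Fewer LRT events enter the formal comparison, because transient events outside the recall window are listed only. The first participant entered in December 2017, so some participants may already have passed these visits; the report should say from when the questions were used. Participants who miss a visit cannot be asked, and the article allows for about 40% drop-out by follow-up, so the number questioned in each arm should be given beside the counts.

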### Data analysis

#### Statistical analysis

Several analytic strategies are planned to test the efficacy of the treatment. First, analyses of variance (ANOVAs) will be conducted to compare the mean outcome in PTSD and depressive symptoms (primary endpoints) as well as the secondary endpoints. The age at the time of trauma, gender, educational level, cognitive status and trauma severity will be considered as covariates.

Secondly, individual growth curves will be analysed, i.e. rates and shapes of change will be examined, and individual growth curves will be compared to investigate differences.

Thirdly, multivariate analyses will be used to test the effect of the treatment with regard to primary and secondary outcomes. In this way, correlations between the outcome measures can be considered. Post hoc analyses will be performed following a significant overall effect.

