We expect that life-review therapy will reduce the symptoms of PTSD and related mental health problems with a large pre-post effect size and to a greater extent than the supportive control group at posttest and 6-months follow-up with a medium-to-large effect size.
2.Which factors moderate the treatment effect, i.e. which factors influence who benefits most from the intervention?

We expect that LRT-HS will have a greater effect in people (a) with more severe symptoms of PTSD, depression, anxiety and/or grief at pretest, (b) with lower positive well-being and posttraumatic growth at pretest, (c) of female gender, (d) with higher cognitive status at pretest, (e) with higher trauma severity, i.e. number of traumatic events, months/years experienced during the Holocaust, as well as traumatic experiences before and after the Holocaust.

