#### Sample size

Previous studies on PTSD treatments found a large mean effect size for PTSD outcomes (controlled *d* = 0.8 with a supportive control group) [26]. Studies on LRT also found a large mean (pre-post) effect size in older individuals with a mental disorder (in most studies depression) (g = 1.3; 19). We rest our sample size calculation on the conservative assumption of a medium-to-large effect size (d = 0.7, corresponds to f = 0.35). The sample size was calculated using G*Power 3.1.0 [27]. Given an α = 0.05 and a test power 1-β = 0.80, a total sample size of *n* = 50 (each group *n* = 25) is required. We assume a rather conservative drop-out rate of about 40% from enrolment to follow-up. Thus, we propose to start with 80 participants at enrolment (i.e. 40 in the LRT and 40 in the control group).

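### Three primary scales, two outcome times and three efficacy strategies are left unranked, while the sample size rests on one effect at alpha 0.05; the one stated gate does not cover the primary ANOVAs

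*Protocol article*

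**What the plan says.** All references are to the protocol article.

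- **Endpoints** (Study outcome measures): "Primary endpoints are PTSD and depressive symptoms". PTSD is measured by the PCL-5. For depression, "The Patient Health Questionnaire (PHQ-9) and the Geriatric Depression Scale (GDS) are used". The three scales are not ranked, and nothing says what follows if the two depression scales disagree. Seven secondary endpoints come after them.
- **Times** (Study objectives): symptoms are expected to fall more under LRT than under the social club "at posttest and 6-months follow-up with a medium-to-large effect size". Neither time is called primary.
- **Analysis** (Statistical analysis): "Several analytic strategies are planned to test the efficacy of the treatment". ANOVAs of primary and secondary endpoints come first, individual growth curves second, and multivariate analyses of primary and secondary outcomes third. The third paragraph ends: "Post hoc analyses will be performed following a significant overall effect".
- **Sample size**: one effect is assumed, a "medium-to-large effect size (d = 0.7, corresponds to f = 0.35"). "Given an α = 0.05 and a test power 1-β = 0.80, a total sample size of" 50 follows, raised to 80 because "We assume a rather conservative drop-out rate of about 40% from enrolment to follow-up".

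**The concern.** A confirmatory trial needs its decisive comparison fixed before the data are seen. Here the text allows several: any of three scales, at either of two times or averaged over both, by any of three methods. With so many routes, the error rate and the power depend on a success rule that the article does not give.

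The one stated safeguard is poorly placed. It stands with the third strategy, so the first-strategy ANOVAs of the primary scales go ahead whatever the multivariate result. The third strategy also covers primary and secondary outcomes together. A difference on a secondary measure, for instance reminiscence style, could therefore help produce the overall effect that opens the post hoc tests. Even a well-placed omnibus gate protects only when no outcome differs. Once one outcome truly differs, the gate tends to open and the other outcomes are no longer protected by it.

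At stake is whether a positive result on, say, one depression scale at one time can be read as confirming efficacy.

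**Working it through.** **Inputs from the article.** Three primary scales; two post-baseline times; alpha 0.05 (whether one- or two-sided is not stated); d = 0.7 (f = 0.35); power 0.80; n = 50; 80 enrolled, 40 per arm; drop-out about 40%.

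**Assumed.** The article gives no correlation between scales or between times. I take 0.3 to 0.8 for both. Tests are two-sided at 0.05 unless stated.

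**1. The article's own figure.** For d = 0.7 and 80% power:

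| Test | Total n |
|---|---|
| Two-sided t test, one time | 68 (power at 25 per arm 0.68) |
| One-sided t test, one time | 52 (power at 25 per arm 0.79) |
| Between-group F, repeated measures, 2 measures, correlation 0.5 | 52 (power at 50: 0.800) |
| Between-group F, repeated measures, 3 measures, correlation 0.6 | 50 |

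So 50 is reproduced, within two participants, by a single repeated-measures or one-sided test. It leaves nothing for multiple primary scales. Completers: 80 × (1 − 0.40) = 48, or 24 per arm.

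**2. Any one of six tests (3 scales × 2 times) suffices, no true effect.** If the tests were independent: 1 − 0.95^6 = 26.5%. With correlation, by simulating six jointly normal test statistics (400,000 draws):

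| Scale and time correlation | At least one significant, either direction | At least one favouring LRT |
|---|---|---|
| 0.3 | 25% | 13% |
| 0.5 | 22% | 11% |
| 0.6 | 20% | 10% |
| 0.7 | 18% | 9% |
| 0.8 | 15% | 7.5% |

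The nominal rate for one test is 5% in either direction and 2.5% in favour of LRT. The last column is therefore 7.5/2.5 = 3 to 13/2.5 ≈ 5 times nominal. If alpha 0.05 were meant one-sided, the rate in favour of LRT would be 13.5–23%, against a nominal 5%.

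**3. One test per scale, averaged over the two times.** This leaves three tests. At scale correlations of 0.4 to 0.7, about 11–13% of null trials have at least one significant result in either direction, and about 5–7% have one favouring LRT. Over 0.3 to 0.8 the either-direction figure is about 10–14%.

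**4. Growth-curve and multivariate tests may also carry the claim.** Adding three slope tests and one multivariate test to the six baseline-adjusted tests (trial simulation, N = 50) gives 21–31% in either direction.

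**5. All six must succeed.** The rate of false claims is below 0.3%. Power at d = 0.7 on every scale and time, with 24 per arm, is about 22% (scale/time correlation 0.4/0.5) to 36% (0.75/0.7). With all 40 per arm analysed at full information, an optimistic bound, it is 56–68%. Both lie below the stated 80%.

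**The case against.** Much can be said on the other side.

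- **No rule is stated.** A reader might infer that a win on any scale, time or method counts as efficacy. The article does not say so, and its hypothesis joins the two times with *and*. This stands: the fault is that the decision is left open, not that a faulty rule was adopted.
- **20% is not the false-claim rate.** A reader might take about 20% from the table as the chance of a false efficacy claim. That figure counts results against LRT as well, covers the univariate tests only, and depends on correlations the article does not give. In favour of LRT the six two-sided tests give roughly half of it.
- **Six separate tests are an assumption.** Quoting f and obtaining n = 50 suggest a repeated-measures ANOVA, hence one test per scale. The inflation is then smaller (step 3) but not gone.
- **The multivariate step should not be over-read.** The article refers to multivariate analyses in the plural. It specifies neither a single ten-variable omnibus test nor unadjusted post hoc tests. Low power for such an omnibus test therefore cannot be charged to the plan.
- **Completers only is pessimistic.** Intention-to-treat analysis, imputation and continued data collection after drop-out are planned, so power in step 5 would be higher than at 24 per arm.
- **A statistical analysis plan may settle this.** Adjustment methods are often left to one, so a missing adjustment is not the finding. But the article does describe the endpoints and the efficacy tests, sets alternatives in parallel, and attaches a gate that does not cover the primary ANOVAs. That much is on the page.

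**Conclusion.** The concern holds as a badly fixed efficacy test: three primary scales, two times and three strategies are unranked, set against a sample size for one effect, with a gate that pools primary and secondary outcomes and leaves the ANOVAs free.

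Its size is conditional on the success rule. If any of six two-sided tests suffices, a false result in favour of LRT arises in about 7.5–13% of null trials, and in about 5–7% with one test per scale. The comparison is 2.5% in both cases, at the assumed correlations. Letting the other strategies carry the claim raises this further. If all six are required, the problem is power and not false claims.

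The documents do not support stating one overall error rate for the plan, because they do not say which rule applies.

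**What to change.** Before any unblinded analysis:

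1. Name one decisive model and one decisive time point for the primary endpoints, and state whether alpha is two-sided.
2. Control the error across the primary scales. One way is a fixed order, for example PCL-5 and then one named depression scale at posttest, then the same two at follow-up, stopping at the first non-significant result. The other is Holm across the three scales at the named time. Which depression scale leads is the sponsor's choice. The GDS was developed for older people, so putting the PHQ-9 first is not self-evident.
3. Report the growth curves, the multivariate analyses and the secondary endpoints as supportive, with estimates and intervals. Do not let an omnibus test of primary and secondary outcomes together gate the primary scales.

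The cost is revised wording and the registry update that the article already promises for protocol changes (Data Availability); no extra assessments are needed. An isolated win on one scale, time or method would no longer be confirmatory. A fixed order keeps the full 0.05 for the first test, but stops if that test fails. Holm costs power per scale: its first step uses 0.05/3, where a two-sided single-time t test at d = 0.7 with 25 per arm has power 0.50, against 0.68 at 0.05 (total n for 80% power: 90 against 68).
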